### Safety

2.9

AE refers to all harmful and unintended reactions caused by medical devices used in clinical trials. Local reactions (predictable AEs) that may occur after treatment with medical devices in clinical trials include bruises, local pain, and burning. An AE that meets the criteria for a SAE will be reported to the IRB. In the case of SAE, appropriate solutions for the number of uses or intensity will be taken by the PI's judgment immediately. If necessary, unblind could be considered by IRB. The occurrence of all AEs will be assessed at each visit. The number and percentage of subjects who experience at least 1 AE will be calculated. Symptoms, date of onset, and duration of expected AEs will be recorded.

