### Statistical analysis

2.8

Data analysis, including the validity evaluation variable, will be performed in the full analysis set group. The per protocol group analysis will be performed as the supplementary analysis. An analysis of covariance using the baseline value of VAS as a covariate will be performed. The ambient mean and standard error, 95% confidence interval, *t* statistic, and *P*-value for change in each group will be determined. Variables for the evaluation of efficacy will also be analyzed in the same manner. In all statistical tests, an α = 0.05 on both sides will indicate a statistically significant difference. All statistical analyses will be performed using the SPSS Statistics for Windows Version 20.0 (IBM Corp., Armonk, NY) software. Last observation carried forward analysis will be used to handle missing data. Safety evaluation will be mainly performed by analyzing the frequency of adverse events (AEs) and serious adverse events (SAEs), which are suspected to be associated with the treatment. The evaluation of safety will be conducted in the safety population. An independent sample *t*-test or Wilcoxon rank-sum test will be performed for the analysis of continuous variables. The McNemar test will be used for the analysis of categorical variables. A chi-squared test or Fisher exact test will be performed to examine the potential association of the treatment with the occurrence of AEs.

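### The adverse event definition requires the device to be the cause, so events judged unrelated drop out before the comparison with sham

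*Protocol article*

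**What the plan says.** The relevant text is in two sections of the protocol article.

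**Section 2.9, Safety**
- Definition: "AE refers to all harmful and unintended reactions caused by medical devices used in clinical trials".
- Expected events: "Local reactions (predictable AEs) that may occur after treatment with medical devices in clinical trials include bruises, local pain, and burning".
- Ascertainment and summary: "The occurrence of all AEs will be assessed at each visit", and "The number and percentage of subjects who experience at least 1 AE will be calculated".
- Detail: "Symptoms, date of onset, and duration of expected AEs will be recorded". This is the only sentence in the article on which details of an event are captured.
- A serious event is an adverse event, as defined, that also meets the seriousness criteria. Such events go to the ethics board.

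**Section 2.8, Statistical analysis**
- Safety is mainly evaluated through the frequency of "adverse events (AEs) and serious adverse events (SAEs), which are suspected to be associated with the treatment", in the safety population.
- A chi-squared or Fisher exact test is planned to "examine the potential association of the treatment with the occurrence of AEs".

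The Introduction makes safety against the sham device part of the trial's objective. The Discussion calls this the first study of the effectiveness and safety of LSM-01.

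**The concern.** A randomised sham arm is there so that nobody has to decide, case by case, whether the device caused an event. All events are counted in both arms, and the difference estimates what the device adds. A definition that admits an event only once it is held to be device-caused puts individual judgement in front of that comparison. Section 2.8 applies a similar filter a second time.

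The setting makes the filter matter. Subjects enter with a VAS of at least 75 mm (section 2.2), and local pain is one of the three expected reactions. When pain worsens after a session, the cause may be the roller or the underlying complaint, and in a single patient the two are hard to tell apart. Events put down to the complaint would leave the safety data, although counting them by arm is what could settle the question.

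An event that was never recorded cannot be recovered at analysis, and the pilot is meant to inform a larger trial.

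**Working it through.** **The plan's own figure.** Section 2.1 takes 12 per group and 20% dropout: 12 / (1 − 0.20) = 15 per group, and 2 × 15 = 30. This reproduces the stated 30, and nothing here disputes it.

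**How far the definition reaches**

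| Element | Where | Uses the causal definition? |
|---|---|---|
| Assessment at each visit | 2.9 | Yes, it uses the term as defined |
| Subjects with at least one event | 2.9 | Yes |
| Serious events sent to the ethics board | 2.9 | Yes, a serious event must first be an adverse event |
| Main safety frequency | 2.8 | Yes, with a further restriction to suspected-related events |
| Chi-squared or Fisher test | 2.8 | Yes through the definition; the further restriction is not repeated |

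Section 2.10 speaks of reactions during trials, a wording based on timing, but it does so for compensation and not for event collection.

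**Effect on the comparison**

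Inputs from the article: 15 per arm (2.3); two-sided α = 0.05 and Fisher exact test (2.8). The article gives no event rates and no attribution shares, so those below are assumptions. For simplicity each subject has at most one event.

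Let p₁ and p₂ be the true risks under LSM-01 and sham, and s₁ and s₂ the shares of events judged device-caused. The recorded risks are p₁s₁ and p₂s₂. The rejection rate is the sum of the two binomial probabilities over all pairs of counts (0 to 15 in each arm) for which the Fisher p-value is at most 0.05.

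*Equal attribution, true risks 40% and 10%*

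| Share attributed | Recorded risks | Difference | Fisher power |
|---|---|---|---|
| 100% | 40% vs 10% | 30 points | 0.325 |
| 75% | 30% vs 7.5% | 22.5 points | 0.204 |
| 50% | 20% vs 5% | 15 points | 0.083 |
| 25% | 10% vs 2.5% | 7.5 points | 0.009 |

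At 50%, the expected number of subjects with an event falls from 15 × 0.40 = 6 to 15 × 0.20 = 3 under LSM-01, and from 1.5 to 0.75 under sham.

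*Equal attribution, no true difference*

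With 40% recorded in both arms the rejection rate is 0.016. With 20% in both (half attributed) it is 0.017. Both are below 0.05, so an equal filter creates no false signal.

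*Unequal attribution, no true difference*

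| True risk, both arms | Shares (LSM-01, sham) | Recorded risks | False difference | Rejection rate |
|---|---|---|---|---|
| 30% | 80%, 30% | 24% vs 9% | 15 points | 0.086 |
| 40% | 90%, 50% | 36% vs 20% | 16 points | 0.076 |
| 40% | 80%, 20% | 32% vs 8% | 24 points | 0.228 |

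These rows need the assessor's judgement to depend on the arm. The article gives no ground for any particular split.

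**The case against.** Four arguments can be made for the plan.

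**Recording of unexpected events.** A reader might infer that details are kept for expected events and no others. The text does not say so. It states that details of expected events are recorded and is silent on the rest. Section 2.9 has all events assessed at each visit, Table 1 schedules safety assessment from V1 after intervention through V7, and the full protocol may list the fields. This stands: loss of detail on unexpected events cannot be asserted. What remains is that the only statement on detail carries the qualifier, which should be removed.

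**Circularity.** A reader might infer that testing association among events selected for association is circular. It is not. The definition speaks of devices used in trials, which can cover the sham as well. Whether a trial device caused an event and whether event frequency differs between randomised arms are separate questions, and with equal attribution the test keeps its error rate. This also stands.

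**Bias between arms.** A reader might infer that events on a non-rotating sham will be attributed less often. That requires the assessor to know or guess the allocation. Section 2.3 describes subjects and investigators as blinded and keeps the trial investigator from operating the device. Section 2.4 claims the same appearance, vibration and sound, and a similar feel. Differential attribution is therefore possible, not established.

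**Weight.** Section 2.8 says mainly, not exclusively, and the test sentence does not repeat the restriction to suspected events. This is a pilot of 30 subjects with two weeks of treatment, of a device already licensed for lumbar muscle pain (2.4), and the Discussion disclaims firm conclusions on effectiveness. These points lower the grade. They do not answer the definition itself, which is explicit, governs every later use of the term, and is not a gap that another document would fill.

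**Conclusion.** The concern holds. As written, the plan removes events judged unrelated to a trial device before the comparison with sham, and every safety summary inherits that filter.

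The loss that needs no failure of blinding is one of events and power. In the assumed example (40% vs 10%, 15 per arm), attributing half of the events in each arm halves the difference from 30 to 15 points and cuts Fisher power from 0.33 to 0.08. Power is low even with complete counting, so the main loss to a pilot is in the description of harms and in the rates carried forward to the larger trial. A false difference arises only if attribution differs by arm.

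All of these sizes rest on assumed event risks and attribution shares. The finding about the definition does not. The primary outcome, the sample size and the efficacy analysis are unaffected. This should be fixed, but the trial's validity does not hang on it.

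**What to change.** - In section 2.9, define an adverse event as any untoward occurrence during the trial, regardless of cause.
- Record symptoms, onset date and duration for every adverse event, expected or not.
- Judge relatedness to the device in a separate field of the case report form.
- In section 2.8, make the between-group comparison on all adverse events in the safety population, and report device-related events as a subset.

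The cost is a few more event entries and ethics board approval of the changed wording, which section 2.10 already requires for modifications. Safety is already assessed at every treatment visit and at V7, so no visit is added, and the sample size stays at 30.

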### Ethics

2.10

This study was designed referencing the Helsinki Declaration and the Korean Clinical Practice Guidelines, and has been approved by the IRB of DUCKMH (number DJUMC-2021-MD-01-1). This study protocol is registered with the Korean National CRIS (CRIS-KCT0006425). In case modifications to the protocol are to be carried out, these modifications will be approved by the IRB. Subjects may be required to withdraw from the study in case of SAEs, and these SAEs will be reported to the IRB. Prior to enrollment, interviews with the subjects will be conducted by a Korean medical doctor to evaluate their suitability for participation in this clinical trial. Monitor will check the records of subjects for the verification of the reliability of clinical trial procedures and data. All data processing will be performed in accordance with the relevant regulations and subject confidentiality will be assured.

Following the occurrence of a SAE, the trial investigator will contact the PI to obtain consent for the release of the blinding. Moreover, this process will be recorded in writing and reported to the IRB within 24 hours. Harmful and unintended reactions during clinical trials of medical devices are compensated in accordance with the Victim Compensation Protocol.

## Discussion

3

More than 80% of the population will suffer from LBP at some point in their lives.^[12]^ For most, the clinical course is benign, with 95% of those afflicted recovering within a few months of onset.^[13]^ However, some will develop chronic LBP. Recurrences of LBP are also common; the incidence rates of subsequent LBP episodes within 1 year for working populations and throughout the lifetime of an individual are 20% to 44% and ≤85%, respectively.^[14]^ For these reasons, there is a growing interest in the development of effective and safe medical devices for the treatment of LBP.

Thus far, this is the first study investigating the effectiveness and safety of LSM-01 (orthopedic machinery) in the treatment of LBP. Because this is a pilot study, the sample size is small and insufficient to yield concrete conclusions regarding the effectiveness of LSM-01. Nevertheless, this pilot clinical trial may provide insights into this treatment modality and evidence for future large-scale clinical trials that will investigate the therapeutic effects of the LSM-01 in individuals with LBP.
